##### Exercise intensity

We intend to perform a moderate-intensity exercise. According to the recommendations of the American Heart Association (www.heart.org), moderate exercise is intended to achieve a heart rate range between 50 and 70% of the maximum heart rate.

The target heart rate range is calculated as follows:(220—age) × 0.5 to (220—age) × 0.7e.g. for a 70-year-old person 75–105 beats per minutee.g. for a 50-year-old person 85–119 beats per minute

The training intensity can be increased up to 75% of the maximum heart rate for participants who are fit enough. The prerequisite for this is that 3 consecutive 30-min sessions have been completed successfully and are free of symptoms. The heart rate is measured before the start of the training and 10 min after the start of the training to ensure an appropriate training intensity.

#### Control group

Patients in the control group receive the in-house physiotherapy standard.

#### Physiotherapy

Physiotherapy is provided by physiotherapists. Both groups receive the same amount of physiotherapy, which includes passive and active mobilisation in bed, standing next to the bed, assisted walking and demonstration of breathing exercises. The physiotherapists have no knowledge of a particular patient’s group assignment and study participation. The target daily duration of physiotherapy is 20 to 30 min, and in individual cases, shorter physiotherapy is performed depending on the general condition of the patient. As soon as the patient is able to walk on level ground for 5 min, can climb one flight of stairs without assistance and there are no pulmonary symptoms, physiotherapy and breathing therapy are terminated.

#### Adverse events

The study involves a low-risk intervention. Special considerations were made in advance to increase the safety of the participants by limiting the maximum age of the participants, the intensity of the exercises and the conduct of the exercises in a seated position. All adverse events will be collected and evaluated.

### Inclusion criteria and exclusion criteria

#### Inclusion criteria

Patients undergoing abdominal surgery due to colorectal carcinoma or liver metastases of colorectal carcinoma at Augsburg University Hospital. Patients must be at least 18 to a maximum of 75 years of age, capable of informed consent, not under legal guardianship and must provide written informed consent. If possible, informed consent will be obtained before the operation in the case of elective or urgent operations. In the case of emergency surgery, the patient will be offered trial participation on postoperative day 1 or as soon as the patient is capable of giving informed consent.

#### Exclusion criteria

Patients who are incapable of giving consent, underage patients, pregnant patients and patients participating in another intervention study that could have a possible influence on the endpoints of this study are excluded from participation. Other exclusion criteria include a history of dementia, schizophrenia, hallucinations, panic attacks or epileptic seizures. Wearers of pacemakers or defibrillators as well as patients taking neuroleptics or antiepileptic drugs are excluded from the study. Patients with active alcohol and/or drug abuse will also be excluded from the study. Further exclusion criteria are heart failure NYHA ≥ 3, COPD ≥ Gold 3, myocardial infarction within the last 3 months, untreated cardiac or pulmonary disease and musculoskeletal conditions that limit the age-appropriate range of motion of the upper body, arms, shoulders and neck.

To ensure adequate exercise capacity, patients who are unable to climb 1 floor without interruption preoperatively (MET (Metabolic Equivalent Threshold) ≥ 4) and are unable to perform light housework/gardening are excluded [36]. Recent studies show that exercise-enhancing video games that require light to moderate exertion correspond to a MET of 2.3 to 3.8 [37]. If there is any doubt about the patient’s statement, the ability to climb stairs is verified under supervision.

#### Secondary exclusion from the VR group

For patients who develop postoperative delirium, the intervention will be paused until the patients are consistently symptom-free and fully orientated for 24 h without drug delirium therapy. Patients with a reduced vigilance will not receive the VR fitness intervention as long as vigilance reduction persists. The VR fitness intervention will be paused while a participant is physically unable to sit in bed or at the side of the bed for 30 min. A new diagnosis of any of the conditions listed under the exclusion criteria will result in exclusion from the intervention group. New onset and continued use of any of the medications listed under the exclusion criteria will result in exclusion from the VR fitness group.

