### Methods against bias

#### Randomisation

The subjects will be randomised preoperatively to one of the two groups (VR fitness/control) in a concealed fashion. Study randomization will be performed through Study Randomizer (2017), a web-based randomization service, after all inclusion and exclusion criteria have been reviewed [38]. Allocation to the study groups is done in a 1:1 ratio. Block randomisation will be performed to ensure equal-sized groups. The size of the individual blocks will only be disclosed after the study has been completed so as not to allow prediction of group allocation. A sufficient number of subjects will be recruited according to the sample size calculation to prevent random errors and to ensure sufficient power to test the hypothesis of the primary endpoint. Randomisation is done by the staff of Augsburg University Hospital who are not involved in data collection and care of the study patients.

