### Sample size calculation

The feasibility study is being carried out with the aim to investigate the clinical and feasibility endpoints of the proposed intervention. Since there is no existing data to enable precise sample size calculations, we adhered to recommendations for sample size calculations in pilot trials. The current postoperative mean length of stay in our own patient population is approx. Thirteen days with a standard deviation of approx. 9.5. A targeted reduction in the length of stay by 2 days would result in a standardized effect size of 0.21. Whitehead et al. recommend a case number of *n* = 28 per group for pilot studies with a standardized effect size of 0.2 and a later planned study with a power of 90% [39]. In order to account for dropouts, e.g. due to non-completed questionnaires or study exclusions, 3 additional patients per group will be recruited. This results in a total number of 62 patients (31 per group).

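### The exclusion rule after randomisation applies to the VR group only; unless it just ends the sessions, it can bias the comparison towards VR

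*Protocol article*

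**What the plan says.** All references are to the Protocol article.

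- **Randomisation:** "The subjects will be randomised preoperatively to one of the two groups (VR fitness/control) in a concealed fashion". On the ratio, the section adds: "Allocation to the study groups is done in a 1:1 ratio".
- **Secondary exclusion from the VR group, temporary rules:** for delirium, "the intervention will be paused until the patients are consistently symptom-free and fully orientated for 24 h without drug delirium therapy". Sessions are also withheld during reduced vigilance and while the patient cannot sit long enough for a session.
- **Secondary exclusion from the VR group, lasting rule for diagnoses:** "A new diagnosis of any of the conditions listed under the exclusion criteria will result in exclusion from the intervention group".
- **Secondary exclusion from the VR group, lasting rule for drugs:** a parallel sentence reads "New onset and continued use of any of the medications listed under the exclusion criteria will result in exclusion from the VR fitness group".
- **Exclusion criteria,** to which the lasting rules refer: among others "myocardial infarction within the last 3 months, untreated cardiac or pulmonary disease", advanced heart failure, hallucinations and epileptic seizures. On drugs, "patients taking neuroleptics or antiepileptic drugs are excluded from the study".
- **Control group:** standard physiotherapy. Neither this section nor any other gives a secondary exclusion rule for controls.
- **Sample size calculation:** the reason "In order to account for dropouts, e.g. due to non-completed questionnaires or study exclusions" is given for adding 3 to the 28 per group, which makes 31 per group and 62 in all.
- **Clinical outcomes:** complications and length of stay are compared between the groups. EQ-5D-5L and distress are measured preoperatively and at 7 and 30 days, and satisfaction at discharge.
- **Discussion:** the control arm is justified by the wish for a better effect-size estimate, and randomisation by the wish to limit selection bias.

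**The concern.** Randomisation makes the two groups comparable only if what happens afterwards does not remove patients from one of them for reasons linked to the outcome. Here the rule acts after allocation and on one arm only, and some of its triggers are linked to the outcomes. A myocardial infarction after surgery is itself a complication, and new neuroleptic use may accompany one. A control patient with the same event stays in the comparison.

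If the VR patient does not, then length of stay, complications, EQ-5D-5L and distress compare a selected VR group with an unselected control group. The difference leans towards VR whenever the removed patients do worse than average. The same distortion passes into the effect size that the pilot is meant to supply for the main trial. If follow-up also stops, the 7- and 30-day questionnaires are lost, and no later analysis plan can recover them.

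**Working it through.** **1. The plan's own figures.** Effect size: 2 / 9.5 = 0.21. Sample size: 28 + 3 = 31 per group, and 2 × 31 = 62. The dropout allowance is 3 / 31 = 9.7% per group. All reproduce and none is in dispute.

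**2. What exclusion means in the text.** Two features point to removal and not just to stopping sessions:
- The section on secondary exclusion uses one wording for interrupting treatment (the intervention is paused or not given) and another for these patients (exclusion from the group).
- The sample size section treats study exclusions as losses that extra recruits must make up. A patient who stays in follow-up and analysis would need no replacement.

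Neither feature is an explicit statement about the analysis set.

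**3. Bias if they are removed.** Inputs: mean stay 13 days, SD 9.5 days and 31 per group, all from the sample size section. Assumptions: no true effect; k of the 31 VR patients are removed; their mean stay is e days above 13. With f = k/31:

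shift in VR mean = [13 − f(13 + e)] / (1 − f) − 13 = −k·e / (31 − k)

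Example, k = 3 and e = 9.5: −3 × 9.5 / 28 = −1.02 days.

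| Removed from VR (k) | e = 4.75 (0.5 SD) | e = 9.5 (1 SD) | e = 19 (2 SD) |
|---|---|---|---|
| 1 | −0.16 | −0.32 | −0.63 |
| 2 | −0.33 | −0.66 | −1.31 |
| 3 | −0.51 | −1.02 | −2.04 |
| 5 | −0.91 | −1.83 | −3.65 |

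With e = 0 the shift is 0, so the bias needs the removed patients to differ from the average. The document gives neither k nor e. Three equals the whole dropout allowance per group, but that allowance also covers other losses, such as incomplete questionnaires.

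**4. Effect on the test.** A simulation used 4,000 runs per setting, 31 per arm, no true effect, Mann–Whitney at two-sided 5%, and log-normal stays with an assumed coefficient of variation of 0.6 within patients who do and do not meet a trigger. Removal was from the VR arm only.

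| Expected share removed | Excess stay | Mean shift (days) | Two-sided rejection rate |
|---|---|---|---|
| 3/31 | 1 SD | −1.01 | 6.3% |
| 3/31 | 2 SD | −1.99 | 7.1% |
| 20% | 1 SD | −2.44 | 12.8% |

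The simulated shifts agree with the formula (−1.02, −2.04 and −2.38).

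**5. After the correction.** If every randomised patient is followed and analysed in the assigned arm, the shift from this rule is 0 and the sample size stays at 62.

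**The case against.** The strongest defence is that the section governs delivery of the VR sessions. On this view its last two sentences mean permanent stopping, as against a temporary pause. They name the intervention group, whereas the exclusion criteria for ineligible patients speak of the study. The dropout allowance is the same in both arms, is not tied to this section, and does not define who is analysed. Analysis populations are commonly left to a full protocol or SAP, which is not shown.

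Much of this stands. A reader might infer that the comparison is already biased as a matter of fact. The document does not support that, because it never says outright that these patients leave the analysis. What survives is that a rule stated here, for one arm only, permits removal and reads most naturally that way. That is a fault in the wording used, not a complaint that an analysis set is undefined.

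Three further inferences go too far:
- **That the VR arm loses its sickest patients.** The triggers are narrower. Cardiac or pulmonary disease counts only if untreated, a drug only if its use continues, and delirium alone leads to a pause. Common surgical complications such as leak or infection are not listed.
- **That the feasibility results are necessarily flattered.** The feasibility outcomes already include discontinued interventions with reasons, and protocol deviations. The risk is confined to whether stopped patients stay in the denominators for retention and compliance.
- **That the bias takes up most of the targeted effect.** Removing 40% of the VR patients in the longest-stay quarter gives about 1.4 days and an 8% chance of a false result favouring VR, against 2.5%. This selects on the outcome itself instead of on the listed triggers, and the 40% has no source in the document.

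It may also be said that this is a pilot with exploratory clinical outcomes. That lessens the weight of a false-positive test. It does not lessen the weight of the effect-size estimate, which the Discussion gives as the reason for having a control arm.

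**Conclusion.** The point holds in conditional form. The protocol states an exclusion rule that acts after randomisation, applies to the VR group only, and is partly triggered by events linked to the outcomes. Together with the dropout wording, its natural reading is that these patients leave follow-up and analysis. If so, the between-group clinical comparisons lean towards VR whenever these patients fare worse than average. If the rule only ends the sessions, this bias is nil.

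The size cannot be known from the document. Assuming stays one SD above the mean, 1 to 5 removals out of 31 shift mean length of stay by about −0.3 to −1.8 days, set against a target of 2 days. One removal would matter little; three would imitate about half of the targeted effect.

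**What to change.** **Secondary exclusion from the VR group:** reword the last two sentences so that a new listed diagnosis, or continued use of a newly started listed drug, ends the VR sessions only. State that the patient:
- stays in the randomised group;
- completes the 7- and 30-day questionnaires and the chart follow-up;
- is analysed in the assigned arm;
- stays in the denominators of the retention and compliance outcomes, recorded as a discontinued intervention with the reason.

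**Sample size calculation:** limit study exclusions, as a reason for dropout, to losses that do not arise from this rule.

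The clinical triggers are not touched and the total stays at 62. The cost is a wording amendment, follow-up of a few more patients, and possibly a slightly less favourable VR result.

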### Methods against bias

#### Randomisation

The subjects will be randomised preoperatively to one of the two groups (VR fitness/control) in a concealed fashion. Study randomization will be performed through Study Randomizer (2017), a web-based randomization service, after all inclusion and exclusion criteria have been reviewed [38]. Allocation to the study groups is done in a 1:1 ratio. Block randomisation will be performed to ensure equal-sized groups. The size of the individual blocks will only be disclosed after the study has been completed so as not to allow prediction of group allocation. A sufficient number of subjects will be recruited according to the sample size calculation to prevent random errors and to ensure sufficient power to test the hypothesis of the primary endpoint. Randomisation is done by the staff of Augsburg University Hospital who are not involved in data collection and care of the study patients.

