### Data analysis plan

Continuous data will be presented as mean ± standard deviation or median with an interquartile range, depending on the distribution. Categorical data will be presented as numbers with percentages. Approximately, normally distributed continuous variables will be compared using the independent *t* test. Non-normally distributed continuous variables will be compared using the Mann–Whitney *U* test. Categorical data will be compared using the *χ*^2^ test. Fisher’s exact test will be used for categorical data if the requirements for *χ*^2^ test are not met. A two-sided *P* < 0.05 is considered significant.

The basic questionnaire used for this study is the validated and standardised EQ-5D-5L health questionnaire of the EuroQol Research Foundation. It will be scored and reported as recommended in the EQ-5D-5L user guide. A questionnaire with additional questions on patient satisfaction (EORTC IN-PATSAT 32) will also be analysed.

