In terms of feasibility, we aim to achieve a minimum participation rate of 70% and a minimum compliance rate of 80% in terms of the completion of questionnaires and participation in the VR sessions offered. Trial participation rates and participation in VR sessions will be analysed during the study. If necessary, the reasons for low attendance rates are analysed and strategies to improve recruitment and participation in the VR sessions offered are discussed with team members.

Although this is a pilot study, we opted for a two-arm design as this provides data from a control, allowing a better understanding of the effect of the study intervention and a more accurate estimate of effect size. Even though randomisation is not a mandatory element of pilot trials we decided to use randomisation to further improve data quality and reduce selection bias. Even though the exercises could be performed by the patient without assistance, we chose to use supervision, to ensure that all exercises are performed correctly, to guarantee adherence to the protocol and to make sure that patients have no problems with the handling of the VR headset. Depending on the results, supervision could be omitted in future trials, if patients are adequately introduced to the system. This could provide an even greater degree of flexibility. The trial intervention could be performed after any abdominal surgery, but we decided to focus on colorectal cancer patients as colorectal cancer surgery is a common procedure and we wanted to ensure a relatively homogeneous patient population.

The proposed pilot study will be the first step to evaluate the feasibility of VR-based interventions in the perioperative period, with the aim of improving the postoperative rehabilitation of cancer patients.

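### The Randomisation section claims sufficient power for a primary-endpoint hypothesis, but the article states neither, and its sample size follows a pilot-trial rule rather than a power calculation for this trial

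*Protocol article*

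**What the plan says.** In the protocol article, the Randomisation section (under Methods against bias) says that the number recruited follows the sample size calculation and is meant "to ensure sufficient power to test the hypothesis of the primary endpoint". This is the article's only mention of a primary endpoint.

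The Sample size calculation section describes something else. Its aim is to "investigate the clinical and feasibility endpoints of the proposed intervention", with no order of priority among them. On method it says: "Since there is no existing data to enable precise sample size calculations, we adhered to recommendations for sample size calculations in pilot trials". It then gives a mean stay of about 13 days "with a standard deviation of approx. 9.5", and continues: "A targeted reduction in the length of stay by 2 days would result in a standardized effect size of 0.21". From a published recommendation it takes n = "28 per group for pilot studies with a standardized effect size of 0.2 and a later planned study with a power of 90" per cent. Three patients per group are added for dropout, which makes 31 per group and 62 in total.

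The Feasibility outcomes and Clinical outcomes sections list outcomes without marking one as primary. Rationale for a pilot trial says that no data exist from which to estimate an effect size. The Data analysis plan compares the groups by t test, Mann–Whitney, chi-squared or Fisher's exact test, and a two-sided P below 0.05 "is considered significant".

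**The concern.** The Randomisation sentence gives the design a property that the other sections do not support. It refers to a primary endpoint, a hypothesis and a power calculation. The article identifies none of the three for this trial.

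The consequence lies in how the results are read. The Data analysis plan sets a significance threshold for between-group tests, and the Rationale asks whether the intervention affects length of stay, complication rates and other clinical outcomes. A reader who has been told that power is sufficient may take a non-significant difference in stay as evidence that the intervention does not shorten it. At this sample size a non-significant result is by far the most likely one even if the full 2-day reduction is real.

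**Working it through.** **Inputs, all from the protocol article**
- Difference in stay: 2 days; standard deviation: 9.5 days; 28 per group before dropout and 31 after (Sample size calculation).
- Allocation 1:1 (Randomisation).
- Two-sided 5% level; t test, or Mann–Whitney if not normally distributed (Data analysis plan).

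**1. The plan's own figures**
- Standardised effect: 2 / 9.5 = 0.2105, stated as 0.21.
- Total: 28 + 3 = 31 per group, and 2 × 31 = 62.

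Both reproduce. The 28 is taken as given from the cited recommendation.

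**2. What the 90% refers to**

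The section attaches it to the later trial. No power figure is given for this one.

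**3. Power of this trial for the 2-day difference, t test**

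The noncentrality parameter is d × √(n/2), with 2n − 2 degrees of freedom.

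| n per group | Noncentrality | Critical t | Power |
|---|---|---|---|
| 28 | 0.2105 × √14 = 0.788 | 2.005 (54 df) | 12.1% |
| 31 | 0.2105 × √15.5 = 0.829 | 2.000 (60 df) | 12.9% |

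If the true difference is 2 days, the chance of a non-significant result is therefore 100 − 12.1 = 87.9% with 28 per group, and 100 − 12.9 = 87.1% with 31.

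**4. Variants**
- Effect of 0.20 instead of 0.2105: 11.4% (28) and 12.1% (31).
- One-sided 5% test, which the plan does not use: 19.3% and 20.5%.
- Skewed stay with Mann–Whitney: with mean 13 and SD 9.5, two standard deviations below the mean is 13 − 19 = −6 days. Stay cannot be negative, so a normal shape is unlikely. Simulation with an assumed lognormal of that mean and SD, and the 2 days applied either as a shift or as a proportional reduction, gives roughly 15 to 22% over 28 to 31 per group.

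**5. Scale**
- Difference detectable with 80% power: 0.762 × 9.5 = 7.2 days (28) or 0.723 × 9.5 = 6.9 days (31).
- Half-width of the 95% interval for the mean difference: 2.005 × 9.5 × √(2/28) = 5.1 days with 28 per group.
- Size needed to detect 2 days by t test: about 355 per group for 80% power and 475 for 90%.

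**The case against.** The strongest reply is that this is openly a pilot. The abstract, Rationale, Sample size calculation and Discussion all say so, low power for clinical outcomes is normal in a pilot, and no computed figure is wrong. All of that stands. It means that the sample size needs no defence. It does not rescue the Randomisation sentence, which says the opposite of what those sections say.

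A second reply is that length of stay is never called primary, so 12% is not the power for the primary endpoint. That is correct. The sentence fails first because the article gives it no endpoint or hypothesis to refer to. The 12% shows only that the one between-group effect with numbers attached cannot support it. The 70% participation and 80% compliance targets in the Discussion do not support it either, since they are called neither primary nor hypotheses.

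A third reply is that the article condenses a fuller protocol, which may name a primary endpoint. Even so, the sentence relies on the sample size calculation, and the calculation shown is not a power calculation for this trial.

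A fourth reply is that the 12% depends on the t test. This is also correct, and the figure should be labelled approximate. Under Mann–Whitney with skewed data it is higher but still low.

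A reader might also infer that the Discussion overclaims when it says that a control arm gives "a more accurate estimate of effect size". The text does not support that reading. The phrase compares a two-arm design with one that has no control, and that comparison is fair.

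**Conclusion.** The power claim in the Randomisation section is wrong as written. It contradicts Rationale for a pilot trial and Sample size calculation, and it refers to a primary endpoint and a hypothesis that the article does not state. For the only between-group effect quantified, power is about 12 to 13% by t test, and roughly 15 to 22% by Mann–Whitney if stay is lognormal. The t-test figures rest on the article's 2 days and SD of 9.5, a two-sided 5% level and 28 to 31 evaluable patients per group. The Mann–Whitney range rests in addition on the assumed distribution. No version examined comes near adequate power.

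Stronger conclusions do not follow. A reader might infer that 62 patients is too few, but the number reproduces and is acceptable for a pilot. A reader might infer that the sponsor means to size the main trial on the effect observed here, but the article does not say so.

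**What to change.** Delete the power claim from the Randomisation section. In its place say that the sample size follows a recommendation for pilot trials and that the trial is not powered for any clinical outcome. Give the figure with its caveat: about 12% by t test for a 2-day difference in stay, approximate because stay is probably skewed. Add that non-significant between-group tests under the Data analysis plan are not evidence of no effect.

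If the section is still to mention a primary outcome, the natural candidates are the feasibility outcomes that already have targets in the Discussion: 70% participation and 80% compliance. That choice is the sponsor's.

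The Discussion needs no rewording on this point, and no commitment is needed on how the main trial will be sized. The cost is a few lines of text. Sample size, allocation, tests and procedures stay as they are.
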